#### Tertiary Outcomes

Tertiary outcomes will evaluate the implementation of the SPPAC program and ensure the SPPAC is delivered as intended. First, the peer trainer will complete a SPPAC checklist for each session, including questions about the logistics of the intervention (eg, time to complete each session, method of contact used) and a list of SPPAC components (eg, goal setting, rewards, skills training). Second, participants in the experimental group will complete a post-SPPAC questionnaire, which asks about attitude about PA, satisfaction with PA, perceived benefits and drawbacks, impact of SPPAC on PA, and changes in views of PA throughout the SPPAC intervention. Third, participants’ reported satisfaction with SPPAC will be collected with the Health Care Climate Questionnaire (HCCQ) [71]. Participants will be asked six questions about their perceived need support from their peer trainer (eg, “My peer trainer listened to how I would like to do things regarding my PA” and “I felt my peer trainer provided me with choices and options about PA”) on a 7-point Likert scale ranging from 1=strongly disagree to 7=strongly agree. High Cronbach alpha levels have been demonstrated [72,73].

### Statistical Analyses

All data analyses are conducted with SPSS version 23. Multiple imputations are used to treat missing data [74]. Data are screened for statistical outliers and assumptions for each statistical test are examined [75].

#### Primary Outcomes

Actigraphy data will be imported into Microsoft Excel in the form of activity counts, then cleaned and entered into SPSS for analysis. A mixed-model ANCOVA will be conducted, controlling for the covariates. Summary statistics (mean, SD), effect size (Cohen *d*), and significance testing (*P*) with 95% confidence intervals will be estimated.

#### Secondary Outcomes

Mixed-model ANCOVA will also be used for significance testing and effect size calculations for all secondary outcome measures. Exploratory analyses will be conducted to investigate the strength and direction of the relationships between the primary and secondary outcomes, looking for moderate-to-strong relationships [76]. If the intervention has a moderate effect on the secondary outcomes and if the secondary outcomes have moderate-to-strong relationships with primary outcome (PA), a potential mediation (exploratory) is suggested.

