### Sample Size

Based on variability data (mean, standard deviation) from Nooijen et al [39], 30 participants will be required to detect a 28-minute difference per day in PA between the experimental group and the control group (beta=.20, alpha=.05). A sample size calculation for ANCOVA in RCT designs was performed using G*power [40]. Because Arbour-Nicitopoulos et al [11] reported a 26% dropout rate in a telephone-delivered PA intervention for people living with spinal cord injury, the sample size was increased accordingly (total N=38).

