Gathering data on the important theoretical variables that are embedded within the SPPAC program will allow for exploration into mediating influences of complex psychological variables that will further our understanding about best strategies for changing PA behaviors in manual wheelchair users. The authors acknowledge the potential burden of the number of self-reported outcomes and the need for two meetings to collect objective PA data. However, it is anticipated that the self-reported outcomes can be completed in approximately 1 hour, and the tester will travel to obtain the Actigraph from the participants (or provide them with a postage-paid envelope for return to the research center) to reduce burden on participants. Future intervention studies can then integrate the most important behavior change determinants to best individualize PA programs for manual wheelchair users.

In addition to psychosocial factors, intervention dose and content represent important variables that need to be considered when promoting PA uptake and maintenance [78]. The Get in Motion program recommended up to 14 sessions of PA counseling over a 6-month period [11]. However, when asked about preferences for the SPPAC program, participants of focus groups (ie, manual wheelchair users, clinicians, and staff of community-based organizations) preferred that the SPPAC program consist of more contacts within a shorter timeframe [34]. The SPPAC program was designed accordingly [34]. In terms of optimal timing for promoting PA, a recent study among individuals with spinal cord injury suggested that the first 2 months are the most critical for successfully promoting PA [78]. However, a recent peer-led manual wheelchair training intervention showed increased participation in meaningful activities among manual wheelchair users up to 25 years after obtaining a manual wheelchair [31].

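### The exploratory mediation screen cannot tell a mediator from a parallel treatment effect or a common cause, and would admit the LTPAQ, itself a measure of PA

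*Protocol article*

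**What the plan says.** The Secondary Outcomes part of Statistical Analyses sets out three steps.

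- Effects on the secondary outcomes: "Mixed-model ANCOVA will also be used for significance testing and effect size calculations for all secondary outcome measures".
- Association with PA: "Exploratory analyses will be conducted to investigate the strength and direction of the relationships between the primary and secondary outcomes", looking for moderate-to-strong ones.
- The screen. Its first condition is "If the intervention has a moderate effect on the secondary outcomes". Its second condition and conclusion are "if the secondary outcomes have moderate-to-strong relationships with primary outcome (PA), a potential mediation (exploratory) is suggested".

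The section gives no number for a moderate effect or a moderate-to-strong relationship. The Discussion says that collecting the theoretical variables "will allow for exploration into mediating influences of complex psychological variables" and so improve understanding of how to change PA behaviour.

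Under Secondary Outcome Measures, the first instrument listed is the LTPAQ, described as self-reported PA. The screen refers to the secondary outcomes without excepting it.

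**The concern.** Mediation by a variable M means that SPPAC changes M and that M in turn changes PA. The second link has to be present among people in the same arm. The screen asks only that M responds to treatment and that M and PA are related. Two other situations meet both conditions:

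- SPPAC raises M and PA by separate routes. Pooled over arms they then correlate through treatment alone.
- An unmeasured factor drives both M and PA, and SPPAC happens to move M, or appears to in a small sample.

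The LTPAQ shows the difficulty plainly. If SPPAC raises PA, self-reported PA should rise and should correlate with accelerometer PA. The screen would then suggest one measure of the outcome as a mediator of another.

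At stake is what the pilot says about mechanism. The primary comparison is not touched.

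**Working it through.** **1. Inputs.** The screen states no figure of its own to reproduce. Sample Size gives the scale: "30 participants will be required to detect a 28-minute difference per day in PA" ("beta=.20, alpha=.05"), raised to 38 for 26% dropout. 30 × 1.26 = 37.8, which gives 38; 38 × 0.74 = 28.1, so about 28–30 people are analysed. The section gives the source of its SD but not the value. With 15 per arm, 80% power and two-sided 5%, the noncentral t gives a detectable standardised effect of d = 1.06 on PA.

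Candidate scores, counted from Secondary Outcome Measures: LTPAQ 1, WST-Q 2, BREQ-2 5, LTPA BSE 1, WheelCon-SF 1, PNSE 3, WhOM 1; total 14.

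Assumptions, because the article gives no values: moderate effect means |d| ≥ 0.5; moderate-to-strong relationship means |r| ≥ 0.3, or more strictly |r| ≥ 0.5; r is pooled over arms; scores correlate 0.3 with each other.

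**2. Correlation produced by treatment alone.** With 1:1 allocation, unit SD within arm and no M–PA link,

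r = (d_M d_Y / 4) / √[(1 + d_M²/4)(1 + d_Y²/4)].

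- d_M = 0.5, d_Y = 1.06: 0.1325 / √(1.0625 × 1.2809) = 0.11
- d_M = 0.8: 0.212 / √(1.16 × 1.2809) = 0.17
- d_M = 1.06: 0.2809 / 1.2809 = 0.22

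This alone falls short of 0.3, but sampling error is large.

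**3. Precision at 30 analysed.**

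- d = 0.5: SE = √(2/15 + 0.25/60) = 0.371; 95% CI −0.23 to 1.23.
- r = 0.3: Fisher z 0.310 ± 1.96/√27; 95% CI −0.07 to 0.60.

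**4. False flags over 14 scores.** Simulation with 15 per arm; a flag needs d and r of the same sign; no score mediates anything. The r cut-off is 0.3 or 0.5.

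| Scenario | At least one flag, 0.3 | At least one flag, 0.5 | Per score, 0.3 | Per score, 0.5 |
|---|---|---|---|---|
| M unaffected, within-arm r 0.4, PA d 1.06 | 51–53% | 35% | 9% | 4% |
| M unaffected, within-arm r 0.3, PA d 0.5 | 43% | 17–18% | 6% | 2% |
| M moved 0.5 SD, PA d 1.06, no M–PA link | 64–65% | 12% | 12% | 1% |
| M moved 0.8 SD, PA d 1.06, no M–PA link | 81% | 22–23% | 24% | 3% |
| Complete null | 11–12% | 0.5–0.6% | 1% | under 0.1% |

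Ranges are differences between simulation runs. With 14 per arm the results are similar.

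One further scenario lies outside these ranges: M moved 0.5 SD, PA d = 1.06, and a non-causal within-arm correlation of 0.3. It gives at least one flag in 96% (cut-off 0.3) or 74% (cut-off 0.5), and per score 41% or 16%.

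**5. Would a significance gate be better?** As a comparator, both paths must be significant, with the M–PA path adjusted for arm. Over the same 14 scores it gives at least one false flag in 28%, 19%, 15% and 29% of trials in the four non-null scenarios, in table order. For one true mediator (d_M = 0.5–0.8, path to PA 0.5, N = 30) it detects 18–39%, against 47–76% for the article's screen at |r| ≥ 0.3. It lowers false flags, misses most true mediators and does not remove confounding: with treatment moving M and a common cause of 0.3–0.5 it still flags a non-mediator in 9–20%.

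**The case against.** A reader might infer that the plan declares mediators, or that it will name false ones in most trials. The documents do not support either.

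- **The claim is hedged.** The text speaks of a potential, exploratory mediation, in a pilot of 38. That is hypothesis generation. This stands and limits the importance of the point.
- **The frequency is not fixed by the article.** A rate above one half depends on taking 0.3 as the cut-off and on counting any flag among 14 scores. At 0.5, none of the four non-null scenarios exceeds 35%, and single-score rates are far lower. This stands too, although a common cause combined with a real effect on M pushes the rates well up.
- **Sampling error is not wholly ignored.** Significance tests are planned for each secondary outcome. The screen's own wording, however, uses only the size of the effect and the strength of the relationship.
- **Detail may sit elsewhere.** Cut-offs, time ordering and intervals are commonly left to a full protocol or SAP, and their absence is not counted here. The point concerns the criterion that is stated: supplying cut-offs would not make it specific to mediation.
- **The use of the result can be overstated.** The Discussion's remark about building important determinants into future studies follows text on participant burden and does not refer to the screen. The pilot's stated use is effect sizes, justification for a later trial and variability data. Nothing says that the next programme will rest on these flags.

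What remains is that the exploratory label lowers the strength of the claim but does not make the criterion informative about mediation.

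**Conclusion.** The point holds in limited form. The screen as worded needs neither an adjusted M–PA link nor an indirect effect, so it cannot distinguish mediation from parallel effects or a common cause at any sample size, and it admits a second measure of PA as a candidate.

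The size is conditional. With |d| ≥ 0.5, 15 per arm and 14 scores inter-correlated 0.3, at least one false flag appears in about 43–81% of trials at |r| ≥ 0.3 and about 12–35% at |r| ≥ 0.5 in the four non-null scenarios. Per score the figures are about 6–24% and 1–4%. The cut-offs, true correlations and pooling over arms are all assumptions. The change is worth making because a better method is available from the same data; it does not bear on the primary analysis.

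**What to change.** Replace the two-condition screen with estimation, for every candidate except the LTPAQ (13 scores on the count above):

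- path a: M at T2 on arm, adjusted for baseline M;
- path b: PA at T3 on M at T2, adjusted for arm, baseline M and baseline PA;
- indirect effect a × b with a bootstrap 95% CI.

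Report all candidates as exploratory estimates, with no yes/no call. An interval-excludes-zero gate is not advised, given the low detection of true mediators by the comparable joint test. If any result still rests only on the two separate associations, describe it as a co-occurring effect and correlation, not as mediation.

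The cost is analysis wording and some programming; the measures are already scheduled at T1, T2 and T3. The downsides are wide intervals at about 30 participants, remaining unmeasured confounding of M and PA, and fewer definite statements about mechanism.

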#### Tertiary Outcomes

Descriptive and content analysis will be used to appraise SPPAC program implementation.

## Results

This project is funded by the Craig H Neilsen Foundation and the Canadian Disability Participation Project. Proposals for additional project funds have been submitted to the Canadian Institute for Health Research (September 2016) and Fonds de Recherche du Santé Québec (December 2016). Two peer trainers have been recruited and trained and pilot evaluation of intervention implementation is currently underway. It is anticipated that enrollment for the proposed study will begin early in 2018, with final results by 2020.

## Discussion

Given the compelling evidence linking PA and quality of life, and the low rates of PA participation among manual wheelchair users, there is a clear need to find strategies to promote PA. On developing a theory-based PA program using the MRC framework, a pilot RCT is a prudent next step [41]. Establishing first effect size estimates for primary and secondary outcomes through a pilot RCT may provide justification for a subsequent efficacy RCT and variability data for future sample size calculations.

The best method to deliver PA interventions for manual wheelchair users is largely unknown. Although community-based telephone-delivered [10,11] and peer-delivered interventions [12] have shown preliminary success in manual wheelchair users, larger studies comparing modalities among this target population are required to determine how to best promote PA. The use of online social media also represents an effective solution for motivating adults without disabilities to participate in PA [33], but the influence of online social support for manual wheelchair users has yet to be evaluated. Grounded in theory, the SPPAC program of research will provide further insight about how peers, telephones, and social media can influence PA uptake and maintenance.

Behavior change is a complex and multifaceted phenomenon with multiple influencing factors. Therefore, successfully changing behavior over the long term requires multilevel interventions that consider individuals within their physical and social environments [77]. Application of two cognitive-based theories (ie, self-determination and social cognitive theories) posits that fulfilling the basic psychological needs (ie, autonomy, relatedness, and perceived control) drives behavior and that self-efficacy (synonymous to perceived control) is a strong and consistent predicator of behavior [15,16]. Therefore, cultivating an autonomy-supportive environment that enhances basic psychological needs, self-efficacy, and motivation through peer support provides a strong theoretical rationale that can effectively increase PA [18,12]. Evidence supports peer-led interventions that are grounded in social cognitive theory, both for improving PA in clinical and nonclinical populations [28] and for improving mobility outcomes for manual wheelchair users [31].

Gathering data on the important theoretical variables that are embedded within the SPPAC program will allow for exploration into mediating influences of complex psychological variables that will further our understanding about best strategies for changing PA behaviors in manual wheelchair users. The authors acknowledge the potential burden of the number of self-reported outcomes and the need for two meetings to collect objective PA data. However, it is anticipated that the self-reported outcomes can be completed in approximately 1 hour, and the tester will travel to obtain the Actigraph from the participants (or provide them with a postage-paid envelope for return to the research center) to reduce burden on participants. Future intervention studies can then integrate the most important behavior change determinants to best individualize PA programs for manual wheelchair users.

In addition to psychosocial factors, intervention dose and content represent important variables that need to be considered when promoting PA uptake and maintenance [78]. The Get in Motion program recommended up to 14 sessions of PA counseling over a 6-month period [11]. However, when asked about preferences for the SPPAC program, participants of focus groups (ie, manual wheelchair users, clinicians, and staff of community-based organizations) preferred that the SPPAC program consist of more contacts within a shorter timeframe [34]. The SPPAC program was designed accordingly [34]. In terms of optimal timing for promoting PA, a recent study among individuals with spinal cord injury suggested that the first 2 months are the most critical for successfully promoting PA [78]. However, a recent peer-led manual wheelchair training intervention showed increased participation in meaningful activities among manual wheelchair users up to 25 years after obtaining a manual wheelchair [31].

Beyond attaining knowledge of important behavioral factors influencing PA uptake and maintenance, the potential benefits of SPPAC include decreased environmental (eg, accessible facilities, transportation) and social barriers (eg, perceived stigma) to PA, limited burden on health care professionals, development of online social supports, and potential cost savings. Moreover, SPPAC has potential for application across age and diagnostic groups, a widespread geographic reach, and allows for a large trainer-to-participant ratio, all which may have time and cost efficiencies in program delivery. Future RCTs may evaluate some of the projected benefits of the SPPAC program.

Foreseen limitations of this study include the heterogeneity of the sample with regard to diagnoses. It is possible that diagnoses (as well as other sociodemographic factors, such as age) may influence the study outcomes. However, the purpose of this pilot study is to provide proof of concept of a novel intervention that may be adopted by manual wheelchair users in general. Future studies may examine diagnoses-specific interventions or consider stratification for various demographic variables. There is also a risk that participants (in both groups) may inadvertently discuss the study with other participants (eg, if they obtain health care services from the same clinic, if they are friends on Facebook) or with testers. Because the intervention is administered by phone on an individual basis, the study itself will not evoke a common meeting place for participants. Moreover, recruitment will target manual wheelchair users in remote geographic locations who may otherwise not have access to community-based programs. To reduce the risk of contamination, peer trainers will remind the participants during each session not to discuss the study with anyone outside of the intervention (including peers/friends or testers).

The SPPAC intervention aims to empower manual wheelchair users to manage their own health through implementation of autonomous supportive environments that also enhance self-efficacy through the use of a peer trainer and mobile phone technology. To our knowledge, no study has evaluated the combined potential of a mobile phone-delivered and peer-led PA intervention for manual wheelchair users. Such an approach may overcome many of the barriers to PA participation within this population, while incorporating important theoretical variables that are associated with behavior change. The SPPAC program has the potential to reach a large number of manual wheelchair users, thus may play an important role in addressing PA behavior change that could have a profound impact on health and health economics.

## Abbreviations

BREQ-2: Behavioral Regulation in Exercise Questionnaire 2
ePARmed-X+PA: electronic Physical Activity Readiness Medical Examination
HADS: Hospital Anxiety and Depression Score
HCCQ: Health Care Climate Questionnaire
IRDPQ: Institut de réadaptation en déficience physique de Québec
IRGLM: Institut de réadaptation Gingras-Lindsay-de-Montréal
ISEL: Interpersonal Support Evaluation List
JRH: Jewish Rehabilitation Hospital
MRC: Medical Research Council
PA: physical activity
PAR-Q+PA: Readiness Questionnaire for Everyone
PNSES: Psychological Need Satisfaction in Exercise Scale
RA: research assistant
RCT: randomized controlled trial
SPPAC: Smartphone Peer Physical Activity Counseling
WheelCon-SF: Wheelchair Use Confidence Scale-Short Form
WhOM: Wheelchair Outcome Measure
WST-Q: Wheelchair Skills Test-Questionnaire

## Appendix

Multimedia Appendix 1 Peer-review reports.
